### Statistical analysis

Analysis will follow standard principles for RCTs. Primary and secondary outcomes will be assessed using two-group comparisons on all participants with evaluable data at 20 week follow-up assessments on an intention-to-treat basis. Statistical significance will be set at *p* < 0.05 for primary outcomes. Statistical significance for secondary outcomes will be defined separately for each suite of analyses prior to analyses being undertaken. Each significance level will be set to account for both type I and type II error rates due to the number of multiple comparisons. Validity of results will be checked using baseline and general descriptive information available for all eligible families. This includes comparing the key characteristics of families who completed the study with those who enrolled in the study but did not complete, and those who did not enrol. The primary outcome measures immediately post-intervention at 20 weeks will be AMPS and rep_max_ of functional strength exercises. Outcomes between treatment groups will be compared at follow-up using linear regression models, where treatment group (intervention or waitlist) and baseline score will be entered in as main effects. Secondary analyses will compare the outcomes between groups for physical activity, participation (CASE and CASP) and QOL (domains of Kidscreen-52).

For reproducibility studies (AMPS, physical activity capacity and performance measures and attention and executive functioning measures), units of variance will be assessed using an analysis of variance (ANOVA) model with Bland Altman Plots with 95 % limits of agreement (LOA). Intra-class correlation coefficients (model: 2-way mixed effects with absolute agreement) and 95 % confidence intervals will be calculated and interpreted as greater than 0.75 as excellent correlation, between 0.4 and 0.75 as adequate and less than 0.40, poor correlation [154]. The SEM will be calculated using [155]:$$ SEM= Standard\  Deviation\ (SD) \times \sqrt{\Big(1-ICC}\Big) $$

The MDC will be calculated using [155]:$$ MDC=SEM \times 1.96 \times \sqrt{2} $$

For attention and executive functioning measures, reliable change indexes (RCI) will be calculated using [156]:$$ RCI=\left( retestscore - initialscore\right)\div \left( standard\  error\  of\  difference,\  SDiff\right) $$

Validity of the ActiGraph accelerometer using oxygen uptake (*V*O_2_) as the criterion measure will be assessed using one-way repeated-measures ANOVA with post-hoc pair-wise comparisons with Bonferroni corrections for multiple comparisons.

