### Design

This study utilises a matched-pairs, randomised waitlist controlled trial (see Fig. 1 for CONSORT flow chart). A matched pairs design was chosen to minimise the risk of baseline between-group differences. A waitlist design ensures that all participants have access to this novel intervention and will facilitate recruitment into the study. Within each pair, each participant will be randomised into either:*Immediate intervention group:* Families return home with Mitii™ equipment and commence training immediately for 20 weeks and then Mitii™ is withdrawn; or*Waitlist delayed intervention (control) group:* Families continue care as usual for 20 weeks, return to Brisbane for a one day re-assessment and then return home with Mitii™ equipment to commence training for 20 weeks. Care as usual includes any therapies (for example, occupational therapy and physiotherapy) usually provided by public or private services and visits to their treating paediatrician or general practitioner. Information about each participant’s usual care during the study period will be gathered using a general study questionnaire. After re-assessment the participants (and their family) will receive the Mitii™ introduction and equipment ready to commence training.

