### Randomisation

Participants will be matched in pairs according to age (18 month age bands) and intelligence quotient (IQ) of ≤80 or >80 (measured on the Wechsler Intelligence Scale for Children – Fourth Edition) [65]. Where available an IQ assessment which has been completed greater than 12 months post injury will be used, otherwise an IQ assessment will be completed prior to matching. Each member of the pair will then be randomly allocated either number “1” or “2” using a computer generated number table. Treatment allocations will be recorded on a piece of folded paper inside a sealed, opaque envelopes and opened (in consecutive order) by independent, non-study personnel. Allocations will read either: “1: Waitlist 2: Immediate”, or “1: Immediate 2: Waitlist”. After the randomisation process is complete, study personnel will be informed of group allocation and information packs will be sent out to families.

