## Statistical analysis

### Sample size

The primary basis for sample size calculation for this study is adequate power (80 %) to detect a clinically important difference for the comparison between the functional effects of Mitii™ (as measured on the AMPS and rep_max_ of functional strength exercises) and usual care at the primary endpoint (20 weeks). This study examines a continuous response variable from matched pairs, waitlist control and immediate-intervention participants with one waitlist control per immediate intervention participant.

In a previous study of Mitii™ in children with unilateral CP (n = 102) the response within each group was normally distributed with SD 0.40 on the AMPS process subscales [49]. To detect a real changes in ADL processing abilities (0.30 units of greater) [92] between groups with 80 % power and α = 0.05, 29 children from each group are required to complete 20 week follow-up assessments.

For rep_max_ of functional strength exercises in a previous reliability study, the response within each subject group was normally distributed with a SD of five sit-to-stand repetitions [93]. If the clinically important difference between groups is four repetitions we will need 26 children from each group to complete 20 week follow-up assessments with, α = 0.05 [47].

Based on a previous RCT using 3T fMRI there were activation in the representative cortex for motor studies with good signal to noise ratio. Participant numbers will allow for some loss of information due to participant refusal (10 %) and scans where motion is a confounder (10 %). To detect fMRI changes between baseline to follow-up assessment (20 weeks) with 80 % power and a SD of 0.65, we will require 39 participants. If the supplementary motor area (SMA) is considered, given coefficients of variation (COV) for control subjects performing motor tasks (COV of 11 % in PM1 and 35 % in SMA, and activation signal of 1.5 %, we will be able to detect differences in percentage activation levels over time as small as 0.47.

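### The primary regression leaves out the matched pairs used for randomisation; the likely effect is conservative inference and some forgone power, not bias or false positives

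*Protocol article*

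**What the plan says.** The Design section states: "This study utilises a matched-pairs, randomised waitlist controlled trial". It gives the reason: "A matched pairs design was chosen to minimise the risk of baseline between-group differences". The Randomisation section sets the matching factors: "Participants will be matched in pairs according to age (18 month age bands) and intelligence quotient (IQ) of ≤80 or >80". One member of each pair goes to each arm.

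The Sample size section keeps the paired description: "This study examines a continuous response variable from matched pairs, waitlist control and immediate-intervention participants". For AMPS process skills it concludes that, to detect the difference "between groups with 80 % power and α = 0.05, 29 children from each group are required to complete 20 week follow-up assessments". The inputs are a difference of 0.30 and an SD of 0.40. For sit-to-stand, a difference of 4 repetitions and an SD of 5 lead to 26 per group.

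The Statistical analysis section describes "two-group comparisons on all participants with evaluable data at 20 week follow-up assessments on an intention-to-treat basis", made with "linear regression models, where treatment group (intervention or waitlist) and baseline score will be entered in as main effects". It mentions no pair effect, matching factor or pair-robust variance for the clinical outcomes. Age enters a model only in the brain-network analysis. The Kidscreen-52 section speaks of comparing children with their matched pair, and the abbreviation list contains generalised estimating equations, but no described analysis uses either.

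**The concern.** Randomising within pairs fixes one child per arm among children alike in age band and IQ group. If such children have similar 20-week outcomes beyond what their own baseline scores explain, the variance of the treatment difference is smaller than a regression on independent children assumes. The stated model then reports intervals that are too wide and p-values that are too large.

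Some residual similarity is plausible. Ages run from 8 to 16, and neither primary outcome is age-normed: one is a raw 30-second repetition count, the other criterion-referenced AMPS logits.

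The protocol names the terms of the model, so this is a stated choice rather than a detail left to a later analysis plan. With 30 children per arm planned and 29 needed for AMPS, there is little slack, so power available without further recruitment is worth having.

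**Working it through.** **Inputs.** From the Sample size section: AMPS process difference 0.30, SD 0.40, 29 per group; sit-to-stand difference 4, SD 5, 26 per group; α = 0.05; power 80%. Assumed: a two-sided test, and a within-pair correlation ρ remaining after baseline adjustment of 0 to 0.3.

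**1. The plan's own figures.** The normal approximation for two independent groups is n = 2(1.96 + 0.84)²/d².
- AMPS: d = 0.30/0.40 = 0.75 gives 28. The exact two-sample t-test gives 28.9, so 29.
- Sit-to-stand: d = 4/5 = 0.80 gives 25. The exact t-test gives 25.5, so 26.

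Both stated figures match the unpaired t-test exactly. No within-pair correlation, which a paired calculation would need, is entered. The section therefore describes matched pairs but calculates as if unpaired.

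**2. Standard error.** With n complete pairs and residual SD σ, the variance of the group difference is 2σ²(1 − ρ)/n. The stated model estimates about 2σ²/n, so its standard error is too large by the factor 1/√(1 − ρ). With σ = 0.40 and n = 29, the model-based value is √(2 × 0.16/29) = 0.105. The actual value is 0.105 at ρ = 0, 0.100 at 0.1, 0.094 at 0.2 and 0.088 at 0.3.

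**3. Type I error.** The actual level is approximately 2[1 − Φ(1.96/√(1 − ρ))].

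**4. Simulation.** 29 complete pairs, residual SD 0.40 after baseline adjustment, difference 0 or 0.30, 4,000 runs per setting. The stated group-plus-baseline model was compared with a fully paired, baseline-adjusted analysis of within-pair differences.

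| ρ | SE factor | Type I, formula | Type I, simulated: stated / paired | Power: stated / paired |
|---|---|---|---|---|
| 0 | 1.00 | 5.0% | 5.4% / 5.3% | 80% / 77% |
| 0.1 | 1.05 | 3.9% | 4.5% / 5.5% | 80% / 81% |
| 0.2 | 1.12 | 2.8% | 2.6% / 4.6% | 82% / 85% |
| 0.3 | 1.20 | 1.9% | 2.0% / 5.2% | 84% / 90% |

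The stated model's mean reported standard error was 0.105 at every ρ. The true spread of its estimate fell from 0.107 (ρ = 0) to 0.101, 0.095 and 0.090, almost the same as the spread under the paired analysis (0.108, 0.103, 0.096, 0.091). The estimate therefore keeps the benefit of matching when pairs are complete; it is the reported precision that is understated.

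**5. Pairs needed if pairing is used (80% power).** AMPS: 30, 28, 25 and 22 at ρ = 0, 0.1, 0.2 and 0.3. Sit-to-stand: 27, 25, 22 and 20.

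**The case against.** The strongest objection is that the residual correlation may be small. Matching is coarse (an 18-month band and a two-level IQ split), and the baseline score already absorbs stable differences due to age and IQ. Suppose the matching factors explain 30% of outcome variance, are shared exactly within pairs, and act only through stable ability. With baseline-outcome correlation r, the residual correlation is 0.30(1 − r)²/(1 − r²) = 0.30(1 − r)/(1 + r). That is 0.30 × 0.4/1.6 = 0.075 at r = 0.6, and 0.30 × 0.14/1.86 ≈ 0.02 at r = 0.86. At such values the stated model is nearly correct. A larger ρ requires age or IQ to predict change itself, which the protocol does not establish. This limits the likely size, but the mismatch between randomisation and model remains.

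It is also fair that matching was chosen for baseline balance, which the analysis does not undo, and that baseline-adjusted regression is a standard method that keeps every child with 20-week data.

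Three stronger readings are tempting, and the document supports none of them:
- **That the precision gained by matching is lost.** With complete pairs the estimate is as precise under either analysis, and the protocol states no interval for the primary comparison that could be called wrong.
- **That false positives rise.** With positive correlation the error goes the other way.
- **That the trial is underpowered because of this.** The sample size and the stated model are both unpaired and agree with each other. Low power appears only if an effect well below the planned 0.75 to 0.80 SD is assumed.

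**Conclusion.** The point holds at moderate severity. The enumerated primary model does not reflect the within-pair randomisation, and the Sample size section describes pairs while calculating without them. The consequence is conservative: for ρ between 0 and 0.3, intervals are up to about 20% too wide, the actual test level may fall to about 2%, and power is up to 6 percentage points below a fully paired analysis (84% against 90% at ρ = 0.3). At ρ = 0 the order reverses, at 80% against 77%.

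The figures rest on the assumed ρ, a two-sided test, 0.40 taken as the residual SD after baseline adjustment, and complete pairs. The values near 0.3 should be read as the upper part of a plausible range, not as an expectation.

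**What to change.** In the Statistical analysis section, add age and IQ group (≤80/>80) as covariates and a random intercept for matched pair to the group-plus-baseline model. A pair-clustered variance is an alternative to the random intercept. State that a child whose partner has no 20-week data stays in the analysis.

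In the Sample size section, state that 29 and 26 per group were computed for an unpaired comparison and take no credit for matching.

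If the present model is kept instead, give the reason and say that it is expected to be conservative. Either choice should be fixed before outcomes are examined by group.

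No new data are needed, since age and IQ are collected for matching. With 58 children, the two covariates (age entered linearly) reduce the residual degrees of freedom from 55 to 53. A fully paired analysis of 29 pairs would leave 27, and its loss of about 3 power points at ρ = 0 is the less favourable case. The proposed mixed model was not itself simulated. It should lose less, because the pair variance can be estimated near zero when age and IQ already explain the similarity within pairs.

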### Secondary hypotheses

Compared to usual care, Mitii™ training will achieve significantly greater:Upper limb activity (unimanual and bimanual), as measured on the Jebsen-Taylor Test of Hand Function (JTTHF), MUUL and the Assisting Hand Assessment (AHA) [56];Lower limb gross motor capacity assessed using the Timed Up and Go (TUG) test, 6-min Walk Test (6MWT) and the High-Level Mobility Assessment Tool (HiMAT);Habitual physical activity (as measured on the ActiGraph® accelerometer) [57];Neurovascular (functional MRI) changes;Visual perception (visual discrimination, visual memory and visual sequential memory) measured on the Test of Visual Perception Skills (TVPS) [58];Executive functioning including information processing, attentional control, cognitive flexibility, goal setting, working memory and behavioural manifestations in everyday life as measured by subtests from the Delis-Kaplan Executive Function System (D-KEFS), the Wechsler Intelligence Scale for Children Fourth Edition (WISC-IV), the Comprehensive Trail Making Test (CTMT), Tower of London – Second Edition and the Behaviour Rating Inventory of Executive Function (BRIEF);Attention including performance on tasks of attention (TEA-Ch) and attention in everyday life as measured by parent rating (Conner’s 3);Psychological functioning as measured by the Strengths and Difficulties Questionnaire (SDQ);Performance and satisfaction with occupational performance goals using the COPM;Participation as measured by the Child and Adolescent Scale of Environment (CASE) and Child and Adolescent Scale of Participation (CASP);QOL on the domains of functioning and participation as measured on the Kidscreen-52;Parent reported functional abilities in self-care and daily activities (using the MobQues28) [59]

Finally, Mitii™ will be more cost-effective compared with usual care as shown by resource use and consequence based on function (AMPS) and QOL (Child Health Utility 9D (CHU-9D) [60] and Kidscreen-52 [61])

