#### Physical capacity and performance test-retest reproducibility and validity

Participants will have the option to participate in test-retest reproducibility study of rep_max_ of functional strength exercises, 6MWT, HiMAT and TUG test over two days at the testing facility during baseline (for the immediate group) or 20 week follow-up assessments (for the waitlist group). Accuracy between hand-timed and videos scores during the HiMAT and TUG test will also be investigated. Testing will be performed in the same order by the same physiotherapist.

Participants will also have the option to participate in the validation for the ActiGraph accelerometer as a measure of physical activity intensity in children and adolescents with an ABI. To validate the ActiGraph accelerometer, participants will be asked to return for one assessment day after they have completed the primary end-point (20 week assessment) for the RCT. For the validity protocol, participants will be asked to rest for a 5–10 min period and then conduct selected light, moderate and vigorous assessment tasks, interspersed with 5–10 min rest periods in a standardised manner. To finish, they will complete a 15 min Mitii™ training program adjusted for their individual capacity. These tasks will be performed whilst wearing an ActiGraph accelerometer, heart rate monitor and a portable indirect calorimeter (MetaMax®). For test-retest reproducibility of the ActiGraph accelerometer, participants will rest for five minutes before conducting selected light, moderate and vigorous assessment tasks, interspersed with 5 min rest period in a standardised manner over the baseline assessment and training days.

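### The only analysis named for ActiGraph validity against oxygen uptake is a repeated-measures ANOVA, which quantifies neither agreement nor association with that criterion (minor)

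*Protocol article*

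**What the plan says.** The section on physical capacity and performance test-retest reproducibility and validity offers participants an optional "validation for the ActiGraph accelerometer as a measure of physical activity intensity in children and adolescents with an ABI". It takes place on one extra day after the 20-week assessment. Children rest, then "conduct selected light, moderate and vigorous assessment tasks, interspersed with 5–10 min rest periods in a standardised manner", and finish with a short Mitii session. They do this "whilst wearing an ActiGraph accelerometer, heart rate monitor and a portable indirect calorimeter", so monitor and criterion are recorded on the same child at the same time.

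The analysis is one sentence at the end of the Statistical analysis section. "Validity of the ActiGraph accelerometer using oxygen uptake" as the criterion measure "will be assessed using one-way repeated-measures ANOVA with post-hoc pair-wise comparisons with Bonferroni corrections for multiple comparisons". The sentence does not say what the ANOVA factor is, what scale the ActiGraph output is on, or what result would count as valid. It attaches no bias estimate, limits of agreement, correlation, regression or classification accuracy.

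The same section does name agreement statistics, but for a different purpose. "For reproducibility studies (AMPS, physical activity capacity and performance measures and attention and executive functioning measures"), it specifies an "analysis of variance (ANOVA) model with Bland Altman Plots with 95 % limits of agreement (LOA") and absolute-agreement intraclass correlations.

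The device also measures a secondary hypothesis: "Habitual physical activity (as measured on the ActiGraph® accelerometer").

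**The concern.** Criterion validity asks how closely the monitor's reading matches, or at least tracks, measured oxygen uptake in the same child doing the same task. A repeated-measures ANOVA compares means across the levels of a factor. It returns neither the size of the error for a child nor the strength of the relation to the criterion.

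What is at stake is the sub-study's own conclusion. The Habitual Physical Activity section cites ActiGraph validity in children with cerebral palsy and in adults with ABI, not in children with ABI. This sub-study is the document's planned evidence for that gap, and the named analysis cannot fill it.

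**Working it through.** The article states no sample size, acceptance limit or power for this sub-study, so there is no figure of the plan's own to reproduce. Participation is optional and the trial recruits 60 children, so n is at most 60. Every effect size, SD and n below is an assumption. The ANOVA can be set up in two ways, and I checked both.

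**Method as factor (ActiGraph estimate versus measured value, task by task).** With two methods the ANOVA reduces to a paired t-test. Assumed inputs:
- true bias d = 0.5 SD of the paired difference;
- two-sided level 0.05/m, where m is the number of Bonferroni comparisons;
- m = 3 (for example one comparison each for light, moderate and vigorous) and m = 6 (for example two tasks at each intensity).

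The miss rate is P(|T| < t_crit), where T is noncentral t with n−1 degrees of freedom and noncentrality d√n.

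Worked case, n=20 and m=3: noncentrality 0.5 × √20 = 2.24; t_crit at level 0.05/3 with 19 df = 2.63; miss rate 63%.

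| n | m = 3 | m = 6 |
|---|---|---|
| 20 | 63% | 73% |
| 30 | 42% | 53% |
| 40 | 26% | 35% |
| 60 | 8% | 13% |

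The miss rate first falls below 20% at n=45 for m=3 and at n=52 for m=6. More comparisons make a non-significant result more likely, so the correction works against detecting bias.

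A simulation shows that the result does not follow agreement (1,000 runs per n; n = 10, 15, 20, 30; assumed means 1.2, 2.0, 3.5 and 5.5 METs for rest, light, moderate and vigorous; Bonferroni over four tasks):
- A monitor with nearly the correct mean but no relation to VO2 within a task shows no significant difference in any task in 94% to 96% of runs. Its limits of agreement in the moderate task are about ±2.3 METs around a mean of 3.5.
- A precise monitor with only 3% bias is flagged as different in 100% of runs.

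**Activity level as factor (rest, light, moderate, vigorous).** Four levels give 4 × 3 / 2 = 6 pairs. The assumed monitor reads 1.5 times too high and has zero within-task correlation with VO2. Its mean bias is about +1.46 METs: the average task mean is 12.2/4 = 3.05; 1.5 × 3.05 = 4.58; the simulated VO2 mean is about 3.11. The ANOVA and all six corrected pairs are significant in 52%, 82%, 95% and 99.6% of runs at n = 10, 15, 20 and 30. A monitor carrying no information on intensity gives a significant ANOVA in only about 5% of runs. On this reading the test does screen out a monitor that is blind to intensity, but it says nothing about closeness to VO2.

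**The case against.** **A reader might infer that an invalid monitor would be declared valid.** The document does not support that. It gives no rule for declaring validity in either direction, so any pass criterion is the reader's. What stands is narrower: no outcome of this ANOVA measures agreement or association with VO2.

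**Discrimination is a relevant property.** The stated aim is to validate the ActiGraph for physical activity intensity, and part of the cerebral palsy evidence cited is about telling walking intensities apart. A within-child comparison across intensities with corrected pairs tests that. This stands, and it is why the ANOVA should be kept. It does not cover the rest of the question, because the sentence names oxygen uptake as the criterion.

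**The article is condensed.** The factor, scale and margin could sit in a fuller document, and their absence alone would not be a finding. But the article does name the validity analysis, and in the same section it names agreement statistics for the neighbouring reproducibility studies only. The point is the method stated.

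**A reader might also infer that the habitual physical activity outcome is undermined.** It is not. The validation is optional, comes after the 20-week endpoint, and nothing makes that outcome conditional on it. The outcome is a randomised between-group comparison, and a scale bias common to both arms would not by itself create a group difference. Absolute intensity levels could be distorted.

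**The simulated monitors are extreme and the inputs assumed.** True. They show what the test can and cannot detect, not how the ActiGraph is likely to behave.

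**Conclusion.** The concern holds as a minor point. The named analysis does not answer the sub-study's criterion-validity question under either set-up: one shows discrimination between intensities, and the other tests mean differences without a margin. The miss rates depend on the assumed 0.5 SD bias, the number of comparisons and n. The underlying conclusion does not depend on them, because an ANOVA of means contains no measure of agreement or association within a child. The consequence is confined to the validity claim for children with ABI. The primary outcomes and the randomised comparison of habitual physical activity are not affected.

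**What to change.** In the ActiGraph validity sentence of the Statistical analysis section, make the main analysis one of agreement or association, using the paired accelerometer and calorimeter data already planned. Two suitable forms:
- If ActiGraph output is converted to METs or VO2: report the mean difference from the measured value with 95% CI and Bland-Altman limits, allowing for repeated tasks per child, against a limit set before analysis.
- If counts stay uncalibrated: fit a mixed model of VO2 on counts with child as random effect, and report the relation with its confidence interval.

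Keep the ANOVA with Bonferroni pairs, label it as a test of discrimination between intensities, and state that activity level is the factor.

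The cost is a little more analysis work and a validity claim that is harder to reach. No new data, visits or participants are needed.
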